## Methods/design

The aim of this trial is to evaluate the non-inferiority of 1 week of brace immobilisation in patients with non- or minimally displaced distal radius fractures. As the ideal treatment of DRF is short, safe and will lead to an early return to work or daily activities, non-inferiority of 1 week of brace immobilisation will be considered superior to a longer period of immobilisation. This hypothesis was also supported by the previous study performed by this study group [22].

Primary outcome is:

Patient-reported outcome measured by the PRWE score after 6 months

Secondary outcomes:

Patient-reported outcome measured by the Quick Disabilities of the Arm, Shoulder and Hand score (qDASH) after 6 weeks and 6 monthsPatient-reported outcome measured by the PRWE score after 6 weeksRange of motion after 6 weeks and 6 monthsPatient-reported pain score (VAS score) at arrival at ED, after cast/brace is applied, in the first week after brace/cast removal, at 6 weeks and 6 monthsRadiological outcome at 6 weeks and 6 monthsComplicationsCost-effectiveness measured by EQ-5D, iMCQ and iPCQ questionnaires

The PRWE is a validated 15-item (scored 1–10) self-reported questionnaire and is the best questionnaire for evaluating the patient-reported outcome in case of DRFs [23, 24]. Patients rate their outcome on a 0–10 scale on pain and functional outcome, and scores will be transformed to a 0–100 score. A higher score indicates greater disability. The DASH Outcome Measure is a validated 30-item self-reported questionnaire for patients with disorders of the arm, shoulder and hand [25, 26]. The QuickDASH (qDASH) is the shortened version of the DASH Outcome Measure, using 11 items instead of 30 (scored 1–5) to measure pain and functional outcome. At least 10 of the 11 items must be completed to calculate a score. The scores will be transformed to a 0–100. A higher score indicates greater disability.

Range of motion will be measured by using a goniometer: volar/dorsal flexion, radial/ulnar deviation and pronation/supination will be determined. Patient-reported pain score will be measured by using the VAS score. VAS score is a widely used method for pain assessments. Patients score their pain on a scale of 1–10. A higher score indicated a higher level of pain. The VAS score will be measured on the ED at arrival and after application of the brace of cast. Patients will also receive a dairy after cast removal to record their pain score.

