Radiological outcome will be measured by the principal investigators of the participating hospitals; data will be cross checked by the clinical investigator; dorsal and volar tilt in degrees, radial height in millimetres and ulnar variance in millimetres will be calculated directly after trauma and after 6 weeks and 6 months. Complications contain secondary displacement (radial shortening > 3 mm, dorsal tilt > 10° or intra-articular step-off > 2 mm), delayed/non-union, re-interventions, complex regional pain syndrome (CRPS), tendon injuries (ruptures and tendinitis), nerve injuries (carpal tunnel syndrome and lesions) and distal radial ulnar joint disability.

Cost-effectiveness and cost-utility of non- or minimally displaced DRFs treated by 3 weeks of cast immobilisation or 1 week of brace immobilisation will be analysed. The perspective of this study is societal, and therefore both direct and indirect costs due to the DRF will be considered. Direct costs will include treatment, follow-up visits at the outpatient clinic, additional visits to health care professionals and the treatment of complications. Non-health care related costs include expenses to travel to and from the hospital. Indirect costs are based on absenteeism of work or loss of working hours due to cast-immobilisation or pain. To estimate health care costs, the friction-cost method will be used to analyse the loss of production for an individual worker. This analysis is based on a cost-effectiveness analysis of a study on the non-operative versus the operative treatment of DRFs [27]. To analyse cost-effectiveness and cost-utility, the EuroQol 5D (EQ-5D), Productivity Cost Questionnaire (iPCQ) and the Medical Consumption questionnaires (iMCQ) will be used [28–31]. Only the applicable items are included in this study. To create baseline data, patients will be asked to complete those questionnaires at the ED at the day of trauma (*t* = 0). Patients will also be asked to complete these questionnaires at 6 weeks and 6 months.

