**Table 2 Tab2:**
[figure not shown]
SPIRIT figure

At each follow-up (FU) visit, the research coordinator or research assistant will ascertain patient status (i.e. secondary interventions, adverse events/complications, deaths) and will verify the information within medical records. All adverse events will be addressed to the principal investigator. The patients will be asked to indicate the actual pain level based on the VAS score, if they are currently treated by a physical therapist and if they returned to work. At 6 weeks and 6 months, the range of motion of the wrist will be measured using a goniometer.

Patients will be asked to complete questionnaires relating to disability (qDASH score and PRWE score) and medical consumption, productivity and general health to analyse cost-effectiveness (EQ-5D, iPCQ, iMCQ). Patients will be asked to complete the questionnaires at the ED as well, to generate baseline data.

Plain X-rays of the wrist will be made at the time of presentation in the hospital at the ED, after 6 weeks and 6 months. The X-ray at 6 months will be taken to determine the grade of degenerative joint changes. Time to define the presence of a delayed- or malunion will be at 6 months. Intention-to-treat principle will be maintained.

Both treatment options and used methods of treatment for this type of fracture are well known. Earlier research did not report any (serious) adverse events. All adverse events will be reported by the investigator; severe adverse events will be reported by the investigator to the sponsor of the study without undue delay after obtaining knowledge of the events. We performed an investigator-initiated risk classification: the risk of this study is expected to be negligible. Therefore, no DSMB/safety committee would be necessary. A monitoring audit will be conducted at the start of the study, after inclusion of the first 10 patients and after finishing the inclusion of patients. Also, a line listing of (serious) adverse events will be kept up and reported annually to the Amsterdam UMC Ethical Board.

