### Statistical analysis

Data from the demographic data collection and the outcome parameters will be cleaned blindly from the treatment data. Data are presented as mean scores with 95% confidence intervals. Linear regression analysis will be performed if data are not normally distributed.

A blinded evaluation of the trial patient’s functional status will be performed by a research assistant by use of the PRWE and qDASH scores. Blinded radiographic evaluation will be performed the intervention group and the control group. An independent expert will assess the degree of dislocation on an X-ray, blinded from the first assessment. Final blinded analysis of the primary outcome parameters will only be performed after 6-month follow-up.

The analysis of this study will be carried out according to the intention-to-treat principle, i.e. the patients will remain in the group they will be randomly allocated to at the baseline. Analysis of functional outcome will be assessed using repeated-measures analysis of variance (GLM 4) with the time as the within-group factor and the treatment as the between-group factor. The post hoc analysis will be performed on the time of randomisation. Group comparisons at different time points will only be made when the overall repeated-measures tests are statistically significant. All scores will be tested for normality using the Kolmogorov–Smirnov test. Parametric variables will be compared using the Student’s *t*-test, while non-parametric and ordinal variables will be compared using the Mann–Whitney *U* statistic. Nominal variables will be compared across independent groups using the chi-squared test or Fisher’s exact test. Homogeneity of variance will be assessed using Levene’s test.

Baseline characteristics that will be analyses are gender, age, dominancy, fracture side, fracture characteristics, smoking and osteoporosis. The outcome will be tested for normality and according to the outcome mean or median baseline characteristics will be compared.

Primary and secondary outcome measures are functional outcome (PRWE and qDASH), return to work, range of motion, pain, radiological outcome, complications and cost-effectiveness.

Missing data of the PRWE and qDASH score during follow-up can be imputed using multiple imputation based on baseline characteristics

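### Alignment and pain are assigned unadjusted two-group tests although the emergency-department values that could sharpen them are already collected

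*Protocol article*

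**What the plan says.** **What is collected.** Methods/design states that dorsal and volar tilt, radial height and ulnar variance "will be calculated directly after trauma and after 6 weeks and 6 months". On pain it states: "The VAS score will be measured on the ED at arrival and after application of the brace of cast". Further VAS scores follow, including at 6 weeks and 6 months. The list of secondary outcomes gives radiological outcome at 6 weeks and 6 months and mentions no change from the first film.

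**How it is analysed.** Under Statistical analysis, "Analysis of functional outcome will be assessed using repeated-measures analysis of variance (GLM 4"), with time and treatment as factors. The same section lists the outcomes as "functional outcome (PRWE and qDASH), return to work, range of motion, pain, radiological outcome, complications and cost-effectiveness". Functional outcome therefore means the two questionnaires, and pain and radiology stand apart from it. The rule left for other continuous outcomes is general: "Parametric variables will be compared using the Student’s" t-test, with the Mann–Whitney test for non-normal or ordinal variables. A later paragraph adds a multivariate analysis of secondary outcomes, to be done only if feasible, and names no covariates.

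**The concern.** A film taken before treatment and a pain score on arrival are baseline measurements of the outcomes later compared between arms. If they predict follow-up, an unadjusted test leaves that predictable part in the error term. Alignment is the clearer case, because displacement is by nature a departure from the first film. The Background calls these fractures stable and the Discussion does not expect secondary dislocation. On that premise, much of the spread in follow-up alignment could be starting position.

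The Background names secondary displacement and pain as the complications that some fear from shorter immobilisation. The trial is sized for PRWE alone, with 34 evaluable patients per arm, so precision on these outcomes is limited to begin with.

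**Working it through.** **Inputs from the article (Sample size calculation).** Margin 10.0, SD 14.0, power 90%, type I error 5%, 34 per arm; 37 per arm after allowance for drop-out.

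**The plan's own figure.** With one-sided 5%: n = 2 × (1.645 + 1.282)² × 14² / 10² = 2 × 8.567 × 1.96 = 33.6, so 34 per arm. The stated figure is reproduced. It concerns PRWE only; the article states no sample size or precision for alignment or pain.

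**Unadjusted comparison at 34 per arm, in SD units.**
- Standard error of the difference: √(2/34) = 0.2425 SD.
- Half-width of the 95% confidence interval: 1.96 × 0.2425 = 0.475 SD.
- Difference detectable with 80% power, two-sided 5%: (1.960 + 0.842) × 0.2425 = 0.68 SD.

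**With a baseline value.** Let r be the correlation between the ED value and the follow-up value. Relative to the unadjusted comparison:
- ANCOVA multiplies the variance by 1 − r², and so the interval width by √(1 − r²). The equivalent number per arm is 34 / (1 − r²).
- A change score, with equal variances at both times, multiplies the width by √(2(1 − r)).

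The article gives no r. The range below is an assumption.

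| r | 1 − r² | ANCOVA width factor | Narrowing | Equivalent n per arm | Detectable difference (SD) | Change-score width factor |
|---|---|---|---|---|---|---|
| 0.2 | 0.96 | 0.98 | 2% | 35 | 0.67 | 1.26 |
| 0.3 | 0.91 | 0.95 | 5% | 37 | 0.65 | 1.18 |
| 0.5 | 0.75 | 0.87 | 13% | 45 | 0.59 | 1.00 |
| 0.7 | 0.51 | 0.71 | 29% | 67 | 0.49 | 0.77 |
| 0.8 | 0.36 | 0.60 | 40% | 94 | 0.41 | 0.63 |

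These are large-sample factors. They ignore the small cost of estimating one slope, which trims the gain slightly and matters only in the top rows.

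**Why ANCOVA and not a change score.** A change score gains only when r exceeds 0.5. At r = 0.2 it widens the interval by 26%, and power for a 0.68 SD difference falls from 80% to 60%. ANCOVA at the same r has 82% power.

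**Which pain score is the baseline.** Only the arrival score qualifies. The score after application of the brace or cast is taken once treatment has started and may already reflect it.

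**The case against.** **The use of raw follow-up levels is inferred.** The article gives a rule for choosing a test and does not say whether the level or the change is tested. The conditional multivariate analysis, or an analysis plan not shown, could add baseline terms. This stands as a caution. The default the article does state is nevertheless an unadjusted two-group test, and neither that rule nor the multivariate sentence names a baseline value.

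**The gain may be small.** ED-arrival VAS is acute injury pain and may say little about pain at 6 weeks or 6 months; r of 0.2 to 0.3 would bring only 2% to 5%. For alignment, the eligibility limits restrict the spread of ED values, and reading by investigators in several hospitals adds error. Both lower r. This stands too, and it is why the range starts at 0.2. Nothing in the article supports treating the high-correlation rows as the expected case.

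**Displacement is already a complication.** It is defined by fixed cut-offs that match the entry limits, so an event means a limit was crossed after entry. That is true, but it does not replace a continuous comparison. On tilt alone, a wrist that moves from 15° volar to 9° dorsal shifts by 24° and is no event; one that moves from 9° to 11° dorsal shifts by 2° and is an event.

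**Stronger readings that the article does not support.**
- A reader might infer that range of motion suffers the same loss, with the other wrist as an unused reference. The article says "At 6 weeks and 6 months, the range of motion of the wrist will be measured using a goniometer" and mentions no reading on the uninjured side, so no collected value is being ignored. The opposite wrist is screened only for fracture, so it need not be a sound reference.
- A reader might infer that dorsal and volar tilt will be analysed as two separate variables. The wording permits that reading but does not state it.
- A reader might infer bias. Under randomisation the unadjusted comparison is unbiased; only precision is at issue.

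**Conclusion.** The point holds for alignment and pain, as lost efficiency on secondary outcomes. The baseline values are collected, and the only tests named for these outcomes do not use them. With 34 analysed per arm the unadjusted comparison detects 0.68 SD with 80% power; ANCOVA would bring this to between 0.67 SD (r = 0.2) and 0.41 SD (r = 0.8). The size rests entirely on an assumed r. The larger gains are plausible for alignment, and the gain for pain may be negligible. The PRWE analysis, the non-inferiority margin and the sample size are untouched. This is a worthwhile improvement to a stated method and does not threaten the trial's main conclusion.

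**What to change.** In Statistical analysis, take alignment and VAS pain out of the general t-test or Mann–Whitney rule and state that:
- tilt at 6 weeks and 6 months is recorded as one signed angle, and tilt, radial height and ulnar variance are each analysed by ANCOVA with the patient's ED-film value and arm as terms;
- later VAS scores are analysed by ANCOVA with ED-arrival VAS and arm as terms, using neither the score after brace or cast application as baseline nor a plain change score;
- results are reported as adjusted mean differences with 95% confidence intervals.

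The cost is a change of wording. No extra visit, measurement or patient is needed. The change should be fixed before outcome data are examined by arm.

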Literature shows that wrist joint stiffness is correlated with a longer period of immobilisation [5, 6]. Wrist stiffness may lead to a restricted range of motion and worse functional outcome. It is believed that stiffness is caused by restricted movement during cast immobilisation over a longer period of time [5]. The ideal treatment of DRF will be short, safe and will lead to an early return to work or daily activities, which is especially important in young and vital patients. In the past, non- or minimally displaced DRFs were immobilised for 4 to 6 weeks [7, 8]. Literature suggests that a shorter period of immobilisation is safe and might even accelerate and enhance functional outcome [9–12]. Recently, a systematic review on the duration of cast immobilisation concluded that a maximum of 3 weeks of cast immobilisation is equal in functional outcome and will not lead to more complications compared with a longer period of immobilisation in both displaced and non-displaced DRFs. Results of this study were limited by strength of available evidence as well as bias. Also, data were too heterogeneous to be pooled to perform a meta-analysis [13]. Beside functional benefits, it is plausible that shortening the period of immobilisation will aid independency and accelerated return to work or school. However, some fear complications such as secondary displacement and pain [9]. Secondary displacement is described as a complication of the non-operatively treated DRF, which occurs in 90% of the cases in the first 2 weeks following trauma, predominantly in displaced and closely reduced DRFs [14, 15]. Secondary displacement in non- and minimally displaced DRFs is very uncommon [3, 10, 16]. Furthermore, two studies stated that the only advantage of cast immobilisation within this group is the antalgic function, which might also support shorter treatment in vital patients [10, 17]. Bracing may provide a comfortable alternative to cast immobilisation. It will allow earlier movement and return to work and might lead to higher patient satisfaction and improvement of cost-effectiveness. Bracing is not related to increased risk of secondary displacement or other complications, as the fractures analysed in this study are non- or minimally displaced and therefore stable fractures. Many studies have been published on functional bracing in DRFs, none providing level 1 evidence [18–20].

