### Sample and selection criteria

The study population is defined as adult patients, between 18 and 50 years old, with a non- or minimally displaced DRF. Patients above the age of 50 are excluded from this study to eliminate bias by osteoporosis.

Inclusion criteria are:18–50 years (to eliminate osteoporosis)Primary non- or minimally displaced DRFIndependent for activities of daily living

Exclusion criteria are:Fracture of the contralateral wristIpsilateral fractures, proximal of the DRFPre-existent abnormalities or functional deficits of the fractured wristOpen fracturesLanguage disability to understand the Dutch patient information and questionnaires

Patients with a non- or minimally displaced DRF will be initially managed on the emergency department (ED) by X-ray and cast immobilisation in a lower arm cast in a neutral position [32]. Non- or minimally displaced will be classified according to the guidelines of the American Association of Orthopedic Surgeons (AAOS) and the Dutch guidelines. They state that the following radiographic parameters do not need a reduction before immobilisation: radial shortening <3 mm, dorsal tilt <10°, volar tilt <20° or intra-articular step-off <2 mm, >15° radial inclination, intact radiocarpal alignment and absence of radial or dorsal/volar translation [4, 34].

Evaluation of eligible patients will take place either at the ED or at the outpatient department of Spaarne Gasthuis, Haarlem/Hoofddorp, Amsterdam UMC, location AMC, Amsterdam and Maasstad Hospital, Rotterdam, the Netherlands. Patients with a DRF will be treated by the physician on call at the ED. Patients are eligible if they meet the in- and exclusion criteria. If a patient is eligible, he/she will start with the standard treatment for non- or minimally displaced DRF, namely cast immobilisation.

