Patients can only participate if the DRF is non- or minimally displaced. They will receive written information and an informed consent form from the attending physician/the clinical investigator/research assistant. When the X-ray taken at the ED showed non- or minimal displacement, informed consent will be signed and eligible patients will be randomised (Fig. 1). An independent research assistant will perform a concealed permuted block randomisation by using a secured computer-generated randomisation schedule after stratification for gender and age. Allocation will be at random in four blocks (Table 1). In total, 1 week of brace immobilisation, if assigned to the intervention group, or 3 weeks of cast immobilisation, if assigned to the control group, will be executed. It is expected that all patients can be included within 1–1.5 year from the start of the study.

**Table 1 Tab1:** Stratification by gender and age

Patient characteristics			Randomisation
List 1	Male	< 30 y.o.a	ABAB AABB ABBA BABA BAAB
List 2	Male	> 30 y.o.a	BAAB BBAA ABAB AABB ABBA
List 3	Female	< 30 y.o.a	AABB ABBA BAAB BBAA BABA
List 4	Female	> 30 y.o.a	ABBA BABA ABAB AABB AABB

*y.o.a.* years of age, *A* 1 week of brace immobilisation, *B* 3 weeks of cast immobilisation

The inclusion and follow-up schedule are visualised in Fig. 2 and Table 2. All patients will be followed for 6 months in total. Assessments will occur at the time of admission at the ED, assessment by phone consult in 1 week after trauma (5–9-day window) in case of inclusion in the intervention group (e.g. 1 week of brace immobilisation), physical assessment in case of the control group (e.g. 3 weeks of cast immobilisation) at 1 (5–9-day window) and 3 weeks (18–24-day window). All patients will be physically assessed at 6 weeks (5–7-week window) and 6 months (5–7-month window) after the start of treatment. After removal of the brace or cast, additional physiotherapy is advised and exercises to train wrist function will be given.

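### Secondary displacement is counted when a film crosses the entry limits, with no minimum change from the ED measurement and no volar limit, so the count does not measure fracture movement

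*Protocol article*

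**What the plan says.** Methods/design lists secondary displacement first among the complications: "Complications contain secondary displacement (radial shortening > 3 mm, dorsal tilt > 10° or intra-articular step-off > 2 mm". Sample and selection criteria describes the fractures that may enter: "radial shortening <3 mm, dorsal tilt <10°, volar tilt <20° or intra-articular step-off <2 mm", with further conditions on inclination, alignment and translation, and attributes the limits to guidelines. Entry is decided on the first film: "When the X-ray taken at the ED showed non- or minimal displacement, informed consent will be signed and eligible patients will be randomised".

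The values needed to calculate change are collected. Methods/design says that dorsal and volar tilt, radial height and ulnar variance "will be calculated directly after trauma and after 6 weeks and 6 months", and the text after Table 2 confirms the films: "Plain X-rays of the wrist will be made at the time of presentation in the hospital at the ED, after 6 weeks and 6 months". Statistical analysis adds a second reading: "An independent expert will assess the degree of dislocation on an X-ray, blinded from the first assessment". None of these places ties the complication to a change from the ED value or to an allowance for reading error. Background says of its frequency: "Secondary displacement in non- and minimally displaced DRFs is very uncommon".

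**The concern.** For the three shared parameters, the event begins where eligibility ends. Two problems follow. A fracture that enters close to a limit and does not move can be read just over it later and be counted. A fracture that moves a long way but stays inside the limits is not counted. A volar shift beyond 20° is outside the entry range, yet on volar tilt alone it can never be an event.

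Background names secondary displacement as one of the complications feared with shorter immobilisation, and asks whether one week in a brace is safe. If true events are very uncommon, one or two spurious events per arm may equal or outnumber them, and the count would say little about whether bracing lets fractures move.

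**Working it through.** The article gives no figure for this outcome, so there is none to reproduce. The check compares the limits and then illustrates their effect under stated assumptions.

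**1. Limits side by side**

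| Parameter | Entry | Event |
|---|---|---|
| Radial shortening | <3 mm | >3 mm |
| Dorsal tilt | <10° | >10° |
| Step-off | <2 mm | >2 mm |
| Volar tilt | <20° | none |

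There is no gap between entry and event. A change from 9.9° to 10.1° dorsal (0.2°) is an event. A change from 19° volar to 9° dorsal (19 + 9 = 28°) is not, nor is a change from 0 to 2.9 mm of shortening.

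**2. One unmoved wrist**

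Assume normal reading error with SD s, independent between films, and an event if either follow-up film exceeds 10°. For true dorsal tilt T, p = 1 − Φ((10 − T)/s) per film and 1 − (1 − p)² over two films. At T = 9°:

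- s = 1°: p = 0.159, two films 0.292
- s = 2°: p = 0.309, two films 0.522
- s = 3°: p = 0.369, two films 0.602

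These apply only to a wrist 1° from the limit. At T = 5° the two-film figures are 0.000, 0.012 and 0.093.

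**3. All entered patients, none moving**

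Assume true tilt uniform from 20° volar to 10° dorsal (the admitted range), with patients kept only if the ED reading lies inside those limits. Simulated share with either follow-up film above 10°:

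| Reading SD | Share | Per arm of 37 |
|---|---|---|
| 1° | 1.7% | 37 × 0.017 ≈ 0.6 |
| 2° | 3.5% | 37 × 0.035 ≈ 1.3 |
| 3° | 5.3% | 37 × 0.053 ≈ 2.0 |

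Sensitivity: with one follow-up film the shares are about 1.0%, 2.0% and 3.1%. With true tilt normal, mean 0° and SD 7°, they are 2.0%, 4.2% and 6.7%. With tilt uniform only from 10° volar to 10° dorsal, they are 5.1% and 7.8% at SD 2° and 3°.

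**4. The same patients, each truly moving 10° dorsally**

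Without reading error, T + 10 exceeds 10 only if T > 0, which is 10 of the 30 admitted degrees, or 33%. With reading SD 2° to 3° and two films, the stated rule flags about 36% to 38%. Nearly two thirds of such shifts go uncounted.

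**5. Would adding a minimum change to the event rule solve it?**

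Take 5° as an illustrative value. Under the uniform model, requiring both the limit and a change of at least 5° lowers the false share to about 0%, 0.8% and 2.8% at SD 1°, 2° and 3°. But a true move from 9° to 13° is detected 97% to 100% of the time under the stated rule at SD 2° to 3°, and only 69% to 78% with the added condition. The 28° shift in step 1 still ends at 9° and is still not counted.

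**The case against.** A reader might infer that the definition ignores the ED film. It does not: only patients whose ED film lies inside the limits are randomised, so every event is a crossing on that patient's own films. What is missing is use of the measured ED value and a minimum change.

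The absolute limit also has a rationale. The selection criteria take it from guidelines as marking fractures that need no reduction, so leaving that category is a meaningful event. This stands, and is the reason to keep the count. Shifts inside the limits are not lost either: tilt, height and variance are a separate radiological outcome measured at all three times. But the article does not say that change from the ED film will be compared, and the complication count does not reflect such shifts. Cross-checking of measurements and the blinded expert reading may reduce error, but neither sets a change threshold.

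A reader might also infer that noise would hide a true excess in the brace arm. That goes too far. If a share f of otherwise event-free patients is falsely counted equally in both arms, the risk difference shrinks only by the factor 1 − f. With f = 5% and assumed true rates of 1% and 10%, the observed rates are 0.05 + 0.95 × 0.01 = 5.95% and 0.05 + 0.95 × 0.10 = 14.5%. The difference falls from 9.0 to 8.55 points; the ratio falls much more, from 10 to about 2.4. Even with perfect measurement, Fisher's exact test with 37 per arm has only about 12% power for 1% against 10%. The trial could not settle this comparison in any case.

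**Conclusion.** The point holds in a limited form. That entry and event limits coincide, that no minimum change is stated, and that volar tilt has no event limit all follow from the text alone. The size does not: 1.7% to 5.3% of unmoved fractures counted on dorsal tilt, or 0.6 to 2 per arm, rests on an assumed reading SD of 1° to 3°, independent errors, an either-film rule and a uniform spread of tilt. Shortening and step-off are not included in that range.

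The documents do not support calling this the trial's main safety outcome. It is one of several listed complications, and the Discussion keeps radiology secondary and does not expect displacement. The primary outcome and sample size are untouched. A fuller definition may exist in the full protocol; the point concerns the definition stated in the article. It is worth correcting because the information needed is already collected.

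**What to change.** Keep the absolute, guideline-based count. Beside it, pre-specify a by-arm comparison of change from the ED film (or of the follow-up value adjusted for the ED value) in dorsal/volar tilt, radial height and ulnar variance at 6 weeks and 6 months.

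Report, as a sensitivity tabulation, how many counted events also exceed a measurement-error amount that the investigators set in advance. This should not replace the event definition, for the reason in step 5 of the working.

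Reconcile volar tilt between Methods/design and Sample and selection criteria: either state how a later volar position or shift is classified as an outcome, or say that it is deliberately left out.

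The cost is some endpoint wording, one extra table and a second displacement figure to interpret. No new films, readers or patients are needed.
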